## Mass drug administration (MDA)

MDA, as the name suggests, consists of the treatment of an entire population with a therapeutic dose for the treatment of the infectious agent, in this case *Plasmodium spp*.

^11^ Despite the notable success of MDA in eliminating malaria from island populations e.g. on Aneityum, Vanuatu,

^12^ to wide-scale implementation in China

^13^ it has fallen out of favour due to concerns over efficacy, cost, and drug resistance. Nevertheless, MDA approaches have been very successful in controlling other neglected tropical diseases and a recent Cochrane review supports the exploration of MDA as another tool in the arsenal in the quest for malaria elimination

^14^. Accordingly, as part of an invigorated approach to achieving local malaria elimination, the National Malaria Control Program with support from PATH MACEPA are evaluating community wide MDA administered through campaigns in Southern Province, Zambia (Step C, Figure 1). MDA with DHAP in conjunction with high levels of vector control have been modelled to be effective over the short term to reduce malaria parasitemia to sufficiently low levels to possibly further achieve elimination with a concomitant routine strategy. A campaign-based MDA approach can be costly and operationally challenging, and for these reasons, maintaining for a prolonged period would be inadvisable. One notable feature of historical MDA campaigns is that resurgence characteristically follows its cessation

^11,14^.

We therefore sought to develop a maximum impact protocol that was sustainable and could be applied either after the cessation of MDA or in an area of low transmission where the cost-benefit of MDA would not apply. This protocol is designed to help test alternative approaches to help optimize the current RFTAT strategy and to align with malaria elimination priorities of the Ministry of Health.

## Rationale for RFDA

The current RFTAT strategy is limited by both the sensitivity of the RDT used to detect asymptomatic infections and the limited chemoprophylaxis provided when using AL. Reactive focal drug administration (RFDA) with dihydroartemisinin-piperaquine (DHAP) could potentially reduce malaria transmission more rapidly. In low transmission settings, low-parasitaemia infections are thought to be increasingly important in sustaining malaria transmission

^15^. In areas with low malaria transmission (<20% parasite prevalence) as much as 80% of malaria infections may not be detectable through microscopy

^16^, which has a similar sensitivity to the RDTs used in the RFTAT intervention

^17^. Only treating individuals who test positive will miss a large portion of the asymptomatic malaria infections in the population. Furthermore, only treating individuals who test positive misses the opportunity to provide chemoprophylaxis to protect the local at-risk population around the incident malaria case. The lack of chemoprophylaxis is the principle reason why screening and treatment campaigns are modeled to be less effective than drug administration campaigns

^18^.

The choice of drug is crucial in providing effective chemoprophylaxis to the at-risk population. Artemisinins have short half-lives that are measured in hours; partner drugs are therefore typically selected for their longer-lasting effects

^19^. The lumefantrine component of AL has a half-life of 4-6 days

^20^. In contrast, the piperaquine component of dihydroartemisinin-piperaquine (DHAP) has a half-life of 28 days or more

^21^. The extended half-life of DHAP will provide increased prophylaxis for individuals receiving RFDA and potentially reduce malaria transmission faster than RFTAT with AL or even RFDA with AL.

## Documenting zero transmission

Documenting zero transmission requires tools that are sufficiently sensitive to declare that local transmission is not occurring. Routine surveillance systems may not be able to provide this level of sensitivity. However, there are two indirect approaches to assess the success of elimination programs and document zero transmission. First, the genetic diversity of the parasites both within infected individuals and within the local human population reflects transmission patterns. As malaria transmission decreases, parasite genetic diversity decreases in the absence of importation. By defining the molecular fingerprint or barcode for each parasite, inferences can be made about the relationship between individual infections and the transmission range and dispersal capacity of the local vector population, as well as the frequency of imported malaria. Genotyping has not yet been used as an outcome to evaluate the effectiveness of malaria interventions but has the potential to be an important piece of evidence to direct elimination efforts and document zero transmission

^22^.

Second, serology can be used to document changes in malaria transmission, and, as such, has been used to confirm malaria elimination from a number of countries, e.g., Greece

^23^. Serological profiling of a target population is fundamentally different to measuring parasite prevalence as it represents the cumulative exposure to the parasite. Seroconversion to any antigen is a function of antigen exposure, antigen immunogencity i.e. its ability to provoke an immune response, and the decay rate of the antibody response. Assuming that all individuals in a population share the same exposure risk, and that the immunogenicity of different parasite strains is comparable, then the likelihood of being seropositive increases with age. By calculating the age-specific seroconversion rates at two time points, one can measure whether transmission has increased or decreased. Traditional anti-malarial antibody serology has focused on total antibody responses, e.g. using whole parasite lysates. This is an excellent approach to document zero transmission, as all immune responses to all parasite antigens are measured as an aggregate. This ensures that exposure is measured with the highest sensitivity and longest exposure history. However immune responses can persist for decades, meaning that an individual may remain seropositive for a prolonged period, even in the absence of any new challenge. This approach is therefore only appropriate for measuring cumulative long-term exposure. Shorter-term changes in exposure can be measured by focusing on specific malaria antigens that have shorter half-lives or are less immunogenic

^24,25^.

The entomological inoculation rate is the best measure of malaria transmission intensity as it directly measures transmission. However finding *Anopheles* mosquitoes in low transmission areas of Southern Province has historically proven difficult making the direct measurement of the entomological inoculation rate impossible. Instead, the entomological inoculation rate can be modeled through measuring serological responses to malaria antibodies to show long-term changes

^25^. Serological responses to anopheline salivary peptides in low transmission settings have proven a suitable surrogate marker to document heterogeneity in mosquito exposure between individuals and locations

^26^.

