### Research Response

In order to assess parasite clearance and the risk of re-infection following a reactive response, a subset of index cases will be randomly selected for follow-up by a research team within each participating health center catchment area (Figure 7). Equal numbers of index cases will be randomly selected in each arm and in each clinic, with a minimum of two index cases per month in each arm i.e. minimum of four total per month. Only index cases reporting no history of travel will be enrolled. A questionnaire will be administered to all individuals participating in the reactive research responses and a finger prick blood sample will be obtained to collect dried blood spots (DBS) for study research purposes only. Participants will be adequately protected with risks minimized as much as possible during sample collection (see Section 3.1 for more information). Information collected through the questionnaire will include demographic information, current symptoms, recent malaria history, travel history, RDT result, HS RDT result (in RFDA arm only) and treatment administered (Appendix 6 and Appendix 7). Geocoordinates will be collected for each household targeted for a reactive response. Blood samples will be used to detect asexual stage parasites by PCR and all positive samples will be genotyped using a molecular bar code.

Follow-up visits will be conducted 3 (Appendix 9), 30 (Appendix 10) and 90 (Appendix 10) days after the initial reactive response. Additional information will be collected from each targeted individual on signs and symptoms of malaria, other treatments received, adherence to the drugs given (if any), and adverse reactions. A finger prick blood sample will be collected from each individual as a DBS at the 30 and 90 day follow-up visits. From the initial reactive response visit, blood samples will be used to detect asexual stage parasites by PCR and all positives genotyped using a molecular bar code.

For research responses enrolled in the RFDA arm, consenting individuals will be tested using the HS RDT as well as the standard RDT. No treatment decisions will be made based on the results from either the HS RDT or the standard RDT, rather they will all be offered DHAP. Individuals who do not consent to be enrolled in the RFDA arm will continue to receive the standard of care i.e. testing with a standard RDT and if positive, treatment given according to national policy.

[figure not shown]

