**Outcomes**: Costs associated with RFTAT and RFDA, including personnel, transportation, and commodities.

**Inclusion/Exclusion criteria:** Not applicable. Study will use cost estimates and estimates of reduction in parasite prevalence as measured in Primary Aim.

**Procedures**: 1) randomization; 2) RFTAT with AL or RFDA with DHAP; 3) follow-up visit on day 3 to assess adverse reactions; 4) measurement of costs

**Analysis**: Detailed tracking of program expenditures on the establishment, production and delivery components of the RFDA and RFTAT interventions, including the value of time spent by the CHWs and other staff, will be used to calculate the financial costs. Costs will be calculated using an ingredients approach that involves enumerating both the quantity of specific inputs (e.g., hours spent, number of rapid diagnostic tests used, etc.) and the time spent during the intervention. As the analysis is intended to be incremental, existing infrastructure and recurrent inputs that would be present in the absence of the intervention will not be costed. The emphasis of the cost analysis is on determining the cost of RFDA and RFTAT alone, and not assessing the cost of training CHWs in the diagnosis and treatment of malaria nor in the follow-up visits to areas receiving reactive responses. Cost-effectiveness will then be measured through incident malaria cases averted as measured through the difference in malaria incidence at health centers in RFDA and RFTAT arms.

### Secondary Aim 4

Measure the proportion of *P. falciparum* infections likely attributable to importation and local transmission using parasite genotyping as well as defining genotypes spatial distribution.

Hypothesis: The proportion of *P. falciparum* infections attributable to importation will increase in both the intervention and control arms as local transmission is interrupted through the reactive case detection strategies. Additionally, the genetic diversity of locally transmitted parasites will decrease as transmission decreases but will be lower in communities receiving RFDA.

**Design**: nested cross-sectional study

**Population**: All individuals with a positive RDT for *P. falciparum* identified in the endline survey and during reactive case detection and their evaluation in reactive research responses.

**Outcomes**: Parasite population genetics, and spatial distribution of defined parasite genotypes.

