**Inclusion/Exclusion criteria:** All individuals tested for malaria during the endline survey as well as during reactive research responses who have consented to further analyses of their dried blood spot sample.

**Procedures**: Sample collection from 1) reactive responses; 2) endline survey; genotyping of PCR-positive samples

**Assays**: Genotyping of *P. falciparum* genomes using PCR-positive DBS

**Analysis**: All malaria infections will be geo-referenced through data collection. Spatial variation in the genomic complexity and diversity will be estimated using the Geneland

^34^package in R

^35^ which uses Bayesian methodology to identify clusters of individuals with similar genotypes while accounting for spatial dependence of geo-referenced data. The procedure is capable of analyzing multivariate gene outcomes including SNPs. The number of separate genetic populations in the study area will be estimated and mapped; migrants (*P. falciparum* infections dissimilar genetically from others in nearby space) will be classified as imported malaria cases without onward transmission and will also be identified and mapped. The influence of a number of environmental factors on the spatial distribution of malaria parasites will be estimated. The enhanced vegetation index available through remotely sensed data will provide an indicator of adult mosquito habitat

^36,37^. A digital elevation model will be used provide an indicator for the propensity of an area to harbor mosquito breeding sites

^38–40^. We aim to utilise spatio-genetic methods that have been utilized in various aspects of ecology, but have not yet been applied to malaria epidemiology to understand transmission dynamics in the two arms

^41^.

Genetic complexity, defined as the number of genetically unique parasites found within health centre and health post catchments, will be compared between RFDA and RFTAT areas using a Poisson or linear regression depending upon the number of genetically unique parasites found. A number of factors will be tested including proximity of the area to the main road, wealth of the area, vector control coverage of the area, age and demographics of the individuals living in the area, as well as environmental factors such as vegetation cover and topographical measures.

### Secondary Aim 5

Assess the utility of serology to measure short-term changes in malaria transmission and evaluate malaria elimination programs

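### Aim 4 hypothesises lower diversity of locally transmitted parasites under RFDA, but the arm comparison counts every unique parasite in the catchment, imported ones included (minor).

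*Protocol*

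**What the plan says.** Section 1.4 (Documenting zero transmission) gives the premise: "As malaria transmission decreases, parasite genetic diversity decreases in the absence of importation".

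The hypothesis of Secondary Aim 4 (Section 2.8.5) has two parts. On importation, it expects that the proportion of "infections attributable to importation will increase in both the intervention and control arms as local transmission is interrupted". On diversity, it says that "the genetic diversity of locally transmitted parasites will decrease as transmission decreases but will be lower in communities receiving RFDA".

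The analysis paragraphs of the same section first describe a spatial genetic analysis. In it, infections that differ genetically from others nearby "will be classified as imported malaria cases without onward transmission and will also be identified and mapped". They then define the measure on which the arms are contrasted: "Genetic complexity, defined as the number of genetically unique parasites found within health centre and health post catchments". The model for this contrast is either Poisson or linear, and the choice rests on how large the counts turn out to be. The factors to be tested cover road proximity, wealth, vector control, demographics and environment. Travel and imported status are not among them.

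Samples come from the endline survey and the research responses. Section 2.4.1 limits research responses to index cases who report no travel. On the data collected in those responses it says: "Information collected through the questionnaire will include demographic information, current symptoms, recent malaria history, travel history". Section 2.5 lists travel history in the endline questionnaire too.

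**The concern.** Section 1.4 makes falling diversity a marker of falling transmission only where nothing is imported. Aim 4 predicts that this condition will hold less and less, and the hypothesis responds by speaking of local parasites only. The regression then drops that restriction: a genotype brought in from elsewhere counts as much as one transmitted locally.

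What is at stake is how the result is read. If RFDA reduces local diversity while imported genotypes keep arriving in both arms, part of the contrast can be masked, and the more local transmission falls, the larger the imported part of what remains. A modest or non-significant ratio could then be reported as little effect on local diversity, which the count does not measure.

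**Working it through.** Aim 4 states no effect size, genotype count or power, so there is no figure to reproduce. L, r, s and q below are illustrative assumptions.

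**Step 1. Does the text restrict the count to local infections?** The hypothesis says local. The count is defined on all unique parasites found. Migrants are classified and mapped, but no sentence takes them out of the count. The no-travel rule covers index cases of research responses, not their neighbours and not endline survey participants. The restriction is therefore partial at most.

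**Step 2. Effect on the ratio.** Let a control catchment have L local genotypes and I imported genotypes not also found locally. Let r be the RFDA/RFTAT ratio of local genotypes, and s = I/(L+I). With the same I in both arms:

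observed ratio = (rL+I)/(L+I) = r(1-s)+s

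| r | s = 0 | 10% | 25% | 50% | 75% |
|---|---|---|---|---|---|
| 0.4 | 0.40 | 0.46 | 0.55 | 0.70 | 0.85 |
| 0.5 | 0.50 | 0.55 | 0.625 | 0.75 | 0.875 |
| 0.7 | 0.70 | 0.73 | 0.775 | 0.85 | 0.925 |

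If RFDA changes the imported count by a factor q, the ratio is r(1-s)+qs, a weighted mean of r and q. The pull toward 1 needs q near 1. With q = r there is no distortion.

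**Step 3. The linear option.** The expected difference is (L+I)-(rL+I) = L(1-r), which does not depend on I. Only the variance grows.

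**Step 4. Power, for illustration.** Take 8 v 8 catchments (Section 2.1), pure Poisson counts, L = 10, r = 0.5 and two-sided 5%. With m0 = 10+I and m1 = 5+I:

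- Poisson: z = |ln(m1/m0)| / sqrt(1/(8·m0)+1/(8·m1)). At I = 0 this is 0.693/0.194 = 3.58, so power = Φ(3.58-1.96) = 95%.
- Linear: z = 5 / sqrt((m0+m1)/8). At I = 0 this is 5/1.37 = 3.65, giving 95.5%.

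| I | s | Ratio | Power, Poisson | Difference | Power, linear |
|---|---|---|---|---|---|
| 0 | 0 | 0.50 | 95% | 5 | 95.5% |
| 3.33 | 25% | 0.625 | 85% | 5 | 86% |
| 10 | 50% | 0.75 | 66% | 5 | 67% |
| 30 | 75% | 0.875 | 37% | 5 | 37% |

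**Step 5. Would a local-only count be enough?** Not alone. Suppose both arms draw on the same 20 equally common local genotypes, with 60 infections genotyped in control and 30 under RFDA. Expected unique genotypes are 20(1-0.95^60) = 19.1 and 20(1-0.95^30) = 15.7. The ratio is 0.82 with no difference in diversity. A plain offset for infections over-corrects: (15.7/30)/(19.1/60) = 1.65. The count has to be compared at a common number of genotyped infections.

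**The case against.** The strongest points on the other side are these.

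- **The count is not the only genetic analysis.** The spatial analysis also estimates complexity and diversity and identifies migrants, and the SAP might say which infections enter the regression. This stands in part. But the protocol defines the count explicitly, and it is the only regression it names for comparing arms on genotypes.
- **Importation is already screened.** The no-travel rule for index cases lowers the imported share in research responses. This stands as mitigation, not removal.
- **Equal imports are not assured.** RFDA offers DHAP to everyone within 140 m whatever the origin of an infection, so imported genotypes at days 30 and 90 may differ by arm. This stands. The bias could then be smaller or of another size, but the count would still not measure local diversity.
- **Import levels are unknown.** This stands. The protocol gives no imported share and does not say how far imported barcodes differ from each other.
- **Aim 4 defines importation by genotype, not by travel.** This stands as a reason to keep a migrant-based version, but only as a sensitivity analysis.

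A reader might infer that the arm difference must shrink, or that a null result is likely. The protocol does not support that: under its linear option the expected difference is unchanged, and under Poisson the shrinkage depends on the imports in each arm. Nor is Section 1.4 in error; it supplies the premise, and the mismatch lies within Section 2.8.5.

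**Conclusion.** The concern holds in limited form. The hypothesis is about locally transmitted parasites, and the arm comparison counts all unique parasites without excluding, stratifying by or adjusting for imported ones. That mismatch is in the text and rests on no assumption.

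Its size does rest on assumptions. With about equal imported genotypes in both arms, a Poisson ratio moves from r to r(1-s)+s; with a linear model the loss is in precision and power only. Severity is minor: it affects one regression in a secondary aim and leaves the primary outcome untouched.

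**What to change.** In the analysis text of Section 2.8.5:

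1. Test the diversity hypothesis on unique parasites among infections in people who report no travel.
2. Account for the number of infections genotyped, for example by comparing counts at a common number of infections (rarefaction), so that the result does not merely reflect fewer infections in one arm.
3. Report the all-parasite count as secondary.
4. Use a count without genotype-defined migrants at most as a sensitivity analysis, because removing dissimilar genotypes lowers diversity by construction.

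The cost is a few sentences and no new samples, since travel history is already collected in the research responses and the endline survey. The questionnaires are not shown, so it should be confirmed that travel is recorded for each sampled person and over what recall period. There are two downsides: fewer infections enter the comparison, and reported travel is an imperfect marker of importation.

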## High sensitivity Alere™ Malaria P.f RDT (HS RDT)

A proportion of *P. falciparum* malaria infections, particularly those that are subclinical, are subpatent. As attention shifts from identifying clinical infections to all infections, the existing diagnostics e.g. microscopy and *Pf* HRP2-based rapid diagnostic tests (RDTs), lack the sensitivity to detect asymptomatic and low density infections (Figure 2)

^27^. For example, microscopy fails to detect a large proportion of *Pf* PCR-positive individuals, up to 20% in high transmission settings and 80% in low transmission settings

^15,28^. Similarly, RDT performance is only marginally better than microscopy and varies greatly depending on the product

^28^. Both of these diagnostics have similar limits of detection of ~100-200 parasites/µL and 800 picograms/mL HRP2 (Figure 2)

^27^. Other tools such as qPCR are highly sensitive and can detect as low as 1 p/µL (Figure 2)

^27^, but lack key attributes required for large-scale field use: ease of use, low cost, short time-to-results, and portability. Thus, to improve the efficiency of active malaria infection detection tactics, new, low cost, and portable tools with improved limit of detection (LOD) are needed

^29^.

[figure not shown]

Figure 2 - Schematic of diagnostic detection limits with respect to parasite and HRP2 density

^27^. Parasite density (black curve) and HRP2 density (red curve) are shown over days prior to treatment and in weeks after treatment. Horizontal lines indicate the detection limits of respective diagnostics. The blue shaded area shows detectability of parasites by microscopy and/or PCR, whereas the red shaded area shows detectability of HRP2 by RDT.

A new generation of diagnostic tests is under development and has a significantly lower LOD. The first of these that will become available in 2017 is the high sensitivity Alere™ Malaria Ag P.f. RDT (HS RDT) for *Pf* HRP2. This test has a tenfold improvement in *Pf* HRP2 LOD from 800 pg/mL to 80 pg/mL, as demonstrated with recombinant *Pf* HRP2 and several native *Pf* HRP2 types from axenic parasite cultures. Further validation of the HS RDT with a panel of clinical specimens from asymptomatic study participants in Myanmar and Uganda show that the order of magnitude of improvement in LOD indicate (1) the ability of the test to reliably detect infections with as low as 1 p/µL as compared to the 50-200 p/µL detected by microscopy or current RDTs and (2) the detection of *Pf* HRP2 as low as 25 pg/mL as compared to 800 pg/mL by current RDTs. The results indicate a significant increase in sensitivity for *Pf* detection in low density subclinical infections with the HS RDT compared to the current commercial RDTs. Furthermore the HS RDT has the same form factor and work flow as current RDTs and therefore has negligible barriers to adoption.

While early studies of this *Pf* HRP2-based HS RDT are highly promising, it has not yet received WHO endorsement as an effective diagnostic tool in ACD strategies and clinical case management. As a result, treatment decisions based on the results from the HS RDT result are inappropriate.

